### **12.8.3 Contraception**

Men must agree not to have sexual intercourse with a woman who is pregnant or breastfeeding a baby from the time of first dosing until the end of the trial without adequate contraception. They also must avoid fathering children during the trial and follow up period. This means that they must not have sex, or if they have sexual intercourse with a female of child-bearing potential, they must use a condom with spermicide, and preferably the female should use some other form of birth control, such as a diaphragm with spermicide, an intrauterine device (IUD), birth control pills, injectable progesterone, sub dermal implants or a tubal ligation for the duration of the trial and follow up period. Women must be of non-childbearing potential [i.e. either postmenopausal or documented hysterectomy – tubal ligation is not sufficient]. For the purposes of this trial, post menopausal is defined as being amenorrhoeic for greater than 2 years with an appropriate clinical profile, e.g. age appropriate, history of vasomotor symptoms. Surgical sterility will be defined as females who have had a hysterectomy and/or bilateral oophorectomy.

## **12.9 Safety**

Clinical safety data is a secondary endpoint of this Phase 2 trial. The safety and tolerability of protocol-specified treatments will be assessed by physical exam findings, 12-lead ECGs recordings, vital sign (blood pressure and heart rate) measurements, clinical laboratory tests, clinical monitoring /observation and spontaneous and elicited adverse event reporting.

## **13 Assessment of Safety**

### **13.1 Safety Reporting Definitions**

The investigator or trial staff are responsible for detecting, documenting and reporting events that meet the definition of an AE or SAE.

AEs will be recorded from the start of IMP dosing V3 (Day1), V4, V5, V6, V7 (Days 14/28/56/84 (All  $\pm$  96h)), V8 (Days 105-111), V9 (Days 109-112) and until the follow-up V10 (Days 120-126).

SAEs will be collected over the same time period as stated above for AEs. However, any SAEs assessed as related to trial participation (e.g. trial treatment, protocol-mandated procedures, invasive tests, or change in existing therapy) or related to a GSK product will be recorded from the time a participant consents to participate in the trial up to and including any follow-up visit. All SAEs will be recorded and reported to sponsor/CI and GSK within 24 hours of awareness, as indicated in TPM.

Investigators are not obligated to actively seek AEs or SAEs in former trial participants. However, if the investigator learns of any SAE, including a death, at any time after a participant has been discharged from the trial, and he/she considers the event reasonably related to the IMP or trial participation, the investigator would promptly notify sponsor/CI and GSK.

#### **13.1.1 Definition of Adverse Events**

An AE is any untoward medical occurrence in a participant or clinical investigation subject, temporally associated with the use of a medicinal product, whether or not considered related to the medicinal product.

Note: An AE can therefore be any unfavorable and unintended sign (including an abnormal laboratory finding), symptom, or disease (new or exacerbated) temporally associated with the use of a medicinal product.

Events meeting the definition of an AE include:

- Any abnormal laboratory test results (haematology, clinical chemistry, or urinalysis) or other safety assessments (e.g., ECGs, radiological scans, vital signs measurements), including those that worsen from baseline, and felt to be clinically significant in the medical and scientific judgment of the investigator.
- Exacerbation of a chronic or intermittent pre-existing condition including either an increase in frequency and/or intensity of the condition.
- New conditions detected or diagnosed after IMP administration even though it may have been present prior to the start of the trial.
- Signs, symptoms, or the clinical sequelae of a suspected interaction.
- Signs, symptoms, or the clinical sequelae of a suspected overdose of either IMP or a concomitant medication (overdose per se will not be reported as an AE/SAE unless this is an intentional overdose taken with possible suicidal/self-harming intent. This should be reported regardless of sequelae.).
- "Lack of efficacy" or "failure of expected pharmacological action" per se will not be reported as an AE or SAE. However, the signs and symptoms and/or clinical sequelae resulting from lack of efficacy will be reported if they fulfill the definition of an AE or SAE.

Events that do not meet the definition of an AE include:

- Any clinically significant abnormal laboratory findings or other abnormal safety assessments that are associated with the underlying disease, unless judged by the investigator to be more severe than expected for the subject's condition.
- The disease/disorder being studied, or expected progression, signs, or symptoms of the disease/disorder being studied, unless more severe than expected for the participants condition.
- Medical or surgical procedure (e.g., endoscopy, appendectomy); the condition that leads to the procedure is an AE.
- Situations where an untoward medical occurrence did not occur (social and/or convenience admission to a hospital).

Anticipated day-to-day fluctuations of pre-existing disease(s) or condition(s) present or detected at the start of the trial that do not worsen.

### **13.1.2 Definition of Serious Adverse Events**

If an event is not an AE as defined in Section 13.1.1, then it cannot be an SAE even if serious conditions are met (e.g., hospitalization for signs/symptoms of the disease under trial, death due to progression of disease, etc).

An SAE is any untoward medical occurrence that:

- Results in death
- Is life-threatening

NOTE: The term 'life-threatening' in the definition of 'serious' refers to an event in which the participant was at risk of death at the time of the event. It does not refer to an event, which hypothetically might have caused death, if it were more severe.

- Requires hospitalisation or prolongation of existing hospitalisation

NOTE: In general, hospitalisation signifies that the participant has been detained (usually involving at least an overnight stay) at the hospital or emergency ward for observation and/or treatment that would not have been appropriate in the physician's office or out-patient setting. Complications that occur during hospitalization are AEs. If a complication prolongs hospitalization or fulfills any other serious criteria, the event is serious. When in doubt as to whether "hospitalisation" occurred or was necessary, the AE should be considered serious.

NOTE: Hospitalisation for elective treatment of a pre-existing condition that did not worsen from baseline V3 is not considered an AE.

- Results in disability/incapacity, or

NOTE: The term disability means a substantial disruption of a person's ability to conduct normal life functions. This definition is not intended to include experiences of relatively minor medical significance such as uncomplicated headache, nausea, vomiting, diarrhea, influenza, and accidental trauma (e.g. sprained ankle) which may interfere or prevent everyday life functions but do not constitute a substantial disruption.

- Is a congenital anomaly/birth defect

- Is associated with liver injury and impaired liver function defined as:
- ALT  $\geq 3 \times \text{ULN}$  and total bilirubin\*  $\geq 2 \times \text{ULN}$  ( $>35\%$  direct), **or** INR  $> 1.5^{**}$  in lieu of bilirubin  $\geq 2 \times \text{ULN}$  ALT  $\geq 3 \times \text{ULN}$  and INR\*\*  $> 1.5$ .

\* Serum bilirubin fractionation should be performed if testing is available; if unavailable, measure urinary bilirubin via dipstick. If fractionation is unavailable and ALT  $\geq 3 \times \text{ULN}$  and total bilirubin  $\geq 2 \times \text{ULN}$ , then the event is still to be reported as an SAE.

\*\* INR testing not required per protocol and the threshold value does not apply to participants receiving anticoagulants. If INR measurement is obtained, the value is to be recorded on the SAE form.

Medical or scientific judgment should be exercised in deciding whether reporting is appropriate in other situations, such as important medical events that may not be immediately life-threatening or result in death or hospitalization but may jeopardize the participant or may require medical or surgical intervention to prevent one of the other outcomes listed in the above definition. These should also be considered serious. Examples of such events are invasive or malignant cancers, intensive treatment in an emergency room or at home for allergic bronchospasm, blood dyscrasias or convulsions that do not result in hospitalization, or development of drug dependency or drug abuse.

## 13.2 Evaluating AEs and SAEs

### 13.2.1 Assessment of Intensity

The investigator will make an assessment of intensity for each AE and SAE reported during the trial and will assign it to one of the following categories:

**Mild:** An event that is easily tolerated by the participant, causing minimal discomfort and not interfering with everyday activities.

**Moderate:** An event that is sufficiently discomforting to interfere with normal everyday activities.

**Severe:** An event that prevents normal everyday activities.

An AE that is assessed as severe will not be confused with an SAE. Severity is a category utilized for rating the intensity of an event; and both AEs and SAEs can be assessed as severe. An event is defined as 'serious' when it meets at least one of the pre-defined outcomes as described in the definition of an SAE.

### 13.2.2 Assessment of Causality

The investigator is obligated to assess the relationship between IMP and the occurrence of each AE/SAE. A "reasonable possibility" is meant to convey that there are facts/evidence or arguments to suggest a causal relationship, rather than a relationship cannot be ruled out. The investigator will use clinical judgment to determine the relationship. Alternative causes, such as natural history of the underlying diseases, concomitant therapy, other risk factors, and the temporal relationship of the event to the IMP will be considered and investigated. The investigator will also consult the IB and/or SmPC, for marketed products, in the determination of their assessment.

For each AE/SAE the investigator must document in the medical notes that they have reviewed the AE/SAE and has provided an assessment of causality.

Causality assessment may be categorized as follows:

- Definitely:** A causal relationship is clinically/biologically certain. This is therefore an Adverse Reaction
- Probable:** A causal relationship is clinically / biologically highly plausible and there is a plausible time sequence between onset of the AE and administration of the investigational medicinal product and there is a reasonable response on withdrawal. This is therefore an Adverse Reaction
- Possible:** A causal relationship is clinically / biologically plausible and there is a plausible time sequence between onset of the AE and administration of the investigational medicinal product. This is therefore an Adverse Reaction
- Unlikely:** A causal relation is improbable and another documented cause of the AE is most plausible. This is therefore an Adverse Event.
- Unrelated:** A causal relationship can be definitely excluded and another documented cause of the AE is most plausible. This is therefore an Adverse Event.

### 13.2.3 Expectedness

An adverse event that has been described as having a causal association with the medicine in the applicable product information (typically the developmental core safety information, DCSI in the IB) in the IB is considered to be an expected event.

When the adverse event is not consistent with the applicable product information this event is considered unexpected.

### 13.3 Expected Serious Adverse Events

Please refer to the safety profile as detailed in the IB, but so far no causal relationship has been suggested in any of the reported AEs or SAEs.

### 13.4 Recording and evaluation of AEs and SAEs

Individual adverse events should be evaluated by the investigator. This includes the evaluation of its seriousness, causality and any relationship between the investigational medicinal product(s) and/or concomitant therapy and the adverse event.

When an AE/SAE occurs, it is the responsibility of the investigator to review all documentation (e.g., hospital progress notes, laboratory, and diagnostics reports) relative to the event. The investigator will then record all relevant information regarding an AE/SAE in the appropriate data collection tool.

The investigator will attempt to establish a diagnosis of the event based on signs, symptoms, and/or other clinical information. In such cases, the diagnosis will be documented as the AE/SAE and not the individual signs/symptoms.

Each Principal Investigator needs to record all adverse events and report these to the Chief Investigator. The Chief Investigator is responsible assessing all AE's and SAEs for expectedness and the prompt notification of all SAEs to the Sponsor. The sponsor has to keep detailed records of all SAEs reported to them by the trial team. For further information please refer to SOP002 pharmacovigilance for investigator teams. This will also be in the TPM.

### Table 6:

| Action                                         | Timeline                                                          |
|------------------------------------------------|-------------------------------------------------------------------|
| Reporting SAE to Sponsor by sending it to CCTU | 24 hours of Investigator awareness                                |
| Reporting SUSAR Sponsor by sending it to CCTU  | 24 hours of Investigator awareness                                |
| Reporting SUSAR to REC & MHRA                  | 7 days – fatal and life threatening
15 days – all others       |
| Returning query responses to CCTU              | As advised in query, depending on the nature of query and urgency |

### 13.5 Reporting of Suspected Unexpected Serious Adverse Reactions (SUSARs)

All suspected adverse reactions related to an investigational medicinal product (the tested IMP and placebo) which occur in this trial, and that are both unexpected and serious (SUSARs) are subject to expedited reporting.

#### 13.5.1 Who should report and whom to report to?

The sponsor delegates the responsibility of notification to the MHRA, REC and any other investigators to the Chief Investigator. As appropriate for investigational therapies in Phase II development, safety and tolerability of Losmapimod will be assessed throughout this trial and reported to the sponsor and GSK.

The Chief Investigator should report all the relevant safety information previously described, to the sponsor, MHRA and to the Ethics Committee concerned. The Chief Investigator shall inform all investigators concerned of relevant information about SUSARs that could adversely affect the safety of patients.

#### 13.5.2 When to report?

##### 13.5.2.1 Fatal or life-threatening SUSARs

The MHRA, Research Ethics Committee, Sponsor and GSK should be notified as soon as possible (ideally between 24 – 72 hours of knowledge) but no later than **7 calendar days** after the trial team and Sponsor has first knowledge of the minimum criteria for expedited reporting.

In each case relevant follow-up information should be sought and a report completed as soon as possible. It should be communicated to the MHRA, Ethics Committee and Sponsor within an additional **8 calendar days**.

##### 13.5.2.2 Non fatal and non life-threatening SUSARs

All other SUSARs and safety issues must be reported to the MHRA and Ethics Committee as soon as possible within 7 calendar days but no later than **15 calendar days** after first knowledge of the minimum criteria for expedited reporting. Further relevant follow-up information should be provided as soon as possible.

#### 13.5.3 How to report?

##### 13.5.3.1 Minimum criteria for initial expedited reporting of SUSARs

Information on the final description and evaluation of an adverse reaction report may not be available within the required time frames for reporting. For regulatory purposes, initial expedited reports should be submitted within the time limits as soon as the minimum following criteria are met:

- a) a suspected investigational medicinal product,
- b) an identifiable participant (e.g. trial subject code number),

- c) an adverse event assessed as serious and unexpected, and for which there is a reasonable suspected causal relationship,
- d) an identifiable reporting source,

and, when available and applicable:

- an unique clinical trial identification (EudraCT number)
- an unique case identification (i.e. sponsor's case identification number).

### **13.5.3.2 Follow-up reports of SUSARs**

In case of incomplete information at the time of initial reporting, all the appropriate information for an adequate analysis of causality should be actively sought from the reporter or other available sources. Further available relevant information should be reported as follow-up reports.

In certain cases, it may be appropriate to conduct follow-up of the long-term outcome of a particular reaction.

### **13.5.3.3 Format of the SUSARs reports**

Electronic reporting is the expected method for expedited reporting of SUSARs to the MHRA. The format and content as defined by the MHRA should be adhered to, please refer to the TPM for further information.

## **14 Toxicity – Emergency Procedures**

No serious toxicity has been seen with Losmapimod. The manufacturer is keen to record all “Sentinel Events” pertaining to liver dysfunction. Therefore, the trial incorporates all safety procedures, in terms of clinical management, as recommended by GlaxoSmithKline. These are detailed below.

In the event of a SAE relating to liver test dysfunction then the following provides guidance on appropriate clinical investigation, from GSK and the regulatory authorities. Should an SAE arise participants will be managed through established NHS clinical pathways as clinically indicated. The trial team and clinical team will, to the best of their ability, undertake the investigations listed below and report these to Sponsor /GSK as safety-related data, but follow local governance procedures at all times.

- Immediately withdraw the participant from IMP
- Notify the medical monitor (as listed on Page 1) within 24 hours of learning of the abnormality to confirm the subject’s IMP cessation and follow-up.
- Complete the “Safety Follow-Up Procedures” listed below.
- Complete the liver event eCRF. If the event also meets the criteria of an SAE (see Section 13.1.2), the SAE data collection tool will be completed separately with the relevant details.
- Upon completion of the safety follow-up withdraw the participant from the trial unless further safety follow up is required.

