### 10.5.1 Biochemistry

Liver chemistry threshold stopping criteria have been designed to assure subject safety and to evaluate liver event aetiology (in alignment with the US Food and Drug Administration premarketing clinical liver safety guidance).

IMP will be stopped for a participant if any of the following liver chemistry stopping criteria is met:

1. ALT  $\geq 3 \times \text{ULN}$  and total bilirubin  $\geq 2 \times \text{ULN}$  ( $>35\%$  direct bilirubin\*);  
\*serum bilirubin fractionation should be performed if testing is available; if unavailable, withdraw subject (if ALT  $\geq 3 \times \text{ULN}$  and total bilirubin  $\geq 2 \times \text{ULN}$ ) and measure urinary bilirubin via dipstick.
2. ALT  $\geq 5 \times \text{ULN}$ .
3. ALT  $\geq 3 \times \text{ULN}$  if associated with symptoms (new or worsening) believed to be related to hepatitis (such as fatigue, nausea, vomiting, right upper quadrant pain or tenderness or jaundice) or hypersensitivity (such as fever, rash or eosinophilia).
4. ALT  $\geq 3 \times \text{ULN}$  persists for  $\geq 4$  weeks.
5. ALT  $\geq 3 \times \text{ULN}$  and cannot be monitored weekly for 4 weeks.

6. Participants with ALT  $\geq 3 \times \text{ULN}$  **and**  $< 5 \times \text{ULN}$  **and** bilirubin  $< 2 \times \text{ULN}$ , who do not exhibit hepatitis symptoms or rash, can continue IMP as long as they can be monitored weekly for 4 weeks. See Section 14. Details on weekly follow-up procedures for these participants.

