### **14.1.1 Safety Follow-Up Procedures for participants with ALT $\geq$ 3xULN and bilirubin $\geq$ 2xULN (>35% direct)**

This event is considered an SAE (see Section 13.1.2). Serum bilirubin fractionation should be performed if testing is available. If fractionation is unavailable, urinary

bilirubin is to be measured via dipstick (a measurement of direct bilirubin, which would suggest liver injury).

- Make every reasonable attempt to have the participants return to the clinic (within 24 hours) for repeat liver chemistries, additional testing and to be monitored closely (with specialist or hepatology consultation recommended).
- Monitor participants twice weekly until liver chemistries (ALT, AST, alkaline phosphatase, bilirubin) resolve, stabilize or return to within baseline values.

**14.1.2 Safety Follow-Up Procedures for participants with ALT  $\geq$  5xULN or ALT  $\geq$  3xULN who have hepatitis symptoms or rash, can't be monitored for 4 weeks or have elevations that persist  $\geq$  4 weeks [Stopping Criteria section 10.5]:**

- Make every reasonable attempt to have the subject return to the clinic within 24-72 hours for repeat liver chemistries and additional testing.
- Monitor participants weekly until liver chemistries (ALT, AST, alkaline phosphatase, bilirubin) resolve, stabilize or return to within baseline values.

**14.1.3 Safety Follow-Up Procedures for participants with ALT  $\geq$  3xULN and  $<$  5xULN and bilirubin  $<$  2xULN, who do not exhibit hepatitis symptoms or rash:**

- Notify the medical monitor within 24 hours of learning of the abnormality to discuss participant safety.
- Participant can continue IMP if liver chemistries (ALT, AST, alkaline phosphatase, bilirubin) can be monitored weekly for up to 4 weeks.
- If at any point these participants meet the liver chemistry stopping criteria (outlined in Section 10.5), immediately withdraw IMP, perform additional testing and continue safety follow-up until liver chemistries resolve, stabilize or return to baseline values.
- After 4 weeks of monitoring, if ALT  $<$  3xULN and bilirubin  $<$  2xULN, participants must be monitored twice monthly until liver chemistries normalize or return to within baseline values.

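### A liver SAE defined by a raised INR meets no stopping criterion in Section 10.5.1, and the protocol does not say whether the permission to continue or the Section 14 instruction to withdraw takes precedence (minor)

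*Protocol*

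**What the plan says.** Four parts of the protocol bear on this case.

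- **SAE definition (13.1.2).** Liver injury with impaired function is serious if ALT is at least 3xULN and total bilirubin is at least 2xULN (more than 35% direct). INR above 1.5 is accepted "in lieu of bilirubin". The footnote limits this: "INR testing not required per protocol and the threshold value does not apply to participants receiving anticoagulants".
- **Stopping list (10.5.1).** Criteria 1 to 5 use ALT, bilirubin, symptoms, persistence for 4 weeks or more, and whether weekly monitoring is possible. None uses INR or SAE status. Item 6 covers ALT from 3 to below 5xULN with bilirubin below 2xULN and says of participants "who do not exhibit hepatitis symptoms or rash, can continue IMP as long as they can be monitored weekly for 4 weeks".
- **Section 14 lead list.** It opens: "In the event of a SAE relating to liver test dysfunction then the following provides guidance on appropriate clinical investigation". Its first bullet is "Immediately withdraw the participant from IMP". A later bullet begins "If the event also meets the criteria of an SAE".
- **Follow-up sections.** 14.1.3 covers the same group as item 6: "Participant can continue IMP if liver chemistries (ALT, AST, alkaline phosphatase, bilirubin) can be monitored weekly for up to 4 weeks". Its only route to stopping is: "If at any point these participants meet the liver chemistry stopping criteria (outlined in Section 10.5), immediately withdraw IMP". It also requires the medical monitor to be notified within 24 hours. A block in 14.1.4 names INR-defined SAEs and requires a prompt return to clinic, twice-weekly chemistries, and trial withdrawal once follow-up is complete unless more follow-up is needed. It gives no instruction on study drug.

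**The concern.** For SAE status the protocol lets a raised INR stand in for raised bilirubin. The bilirubin branch is carried through: it is stopping criterion 1 and has its own follow-up section, 14.1.1. The INR branch has neither. A site that opens 10.5.1 to decide whether to stop the drug would find no criterion met and an explicit permission to continue, for a participant whom 13.1.2 classes as having impaired liver function. What is at stake is that participant's safety. No endpoint, estimate or analysis population is materially affected.

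**Working it through.** **The case.** ALT at least 3 and below 5xULN for under 4 weeks; bilirubin below 2xULN; no hepatitis or hypersensitivity symptoms; weekly monitoring possible; no anticoagulant; an INR that happens to have been measured and is above 1.5.

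**Tracing the rules**

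| Provision | Applies? | Consequence for study drug |
|---|---|---|
| 13.1.2 | Yes, through INR | Event is a liver SAE |
| 10.5.1 criterion 1 | No, bilirubin below 2xULN | – |
| 10.5.1 criterion 2 | No, ALT below 5xULN | – |
| 10.5.1 criterion 3 | No symptoms | – |
| 10.5.1 criterion 4 | Elevation under 4 weeks | – |
| 10.5.1 criterion 5 | Weekly monitoring possible | – |
| 10.5.1 item 6 | Yes | May continue |
| Section 14 lead list, triggered by its lead-in | Yes | Withdraw at once |
| Section 14 lead list, triggered only by stopping criteria | No | No immediate stop anywhere |
| 14.1.1 and 14.1.2 | No | – |
| 14.1.3 | Yes | May continue; override looks only to Section 10.5 |
| 14.1.4 SAE block | Yes, names INR | Silent |

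Item 6 sends the reader to Section 14, and 14.1.3 sends the reader back to Section 10.5. INR appears in neither of those two provisions.

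The Section 14 trigger can be read in two ways. The lead-in names liver SAEs. The later bullet that treats SAE status as something the event may *also* have suggests a list written for stopping-criterion events. On the first reading, an instruction to withdraw stands beside a permission to continue. On the second, the protocol has no immediate stop for this SAE.

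**How often it could arise**

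Inputs: Section 11.2.2 gives ALT of at least 3xULN in 12 (0.9%) on losmapimod and 3 (0.5%) on placebo. Section 16.4 gives about 30 per arm.

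- Expected number with ALT of at least 3xULN from any cause: 30 × 0.009 + 30 × 0.005 = 0.27 + 0.15 = 0.42 of 60.
- Approximate denominators: 12/0.009 = 1333 and 3/0.005 = 600. Exact 95% limits are 0.466% to 1.567% and 0.103% to 1.454%.
- Range: 30 × (0.00466 + 0.00103) = 0.17 to 30 × (0.01567 + 0.01454) = 0.91.

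This counts every ALT elevation of that size, so it bounds the disputed case from above. The protocol gives no share for the disputed case. Purely as an illustration, with an assumed share *s* of those elevations:

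| Assumed *s* | Expected participants | Chance of at least one |
|---|---|---|
| 1% | 0.42 × 0.01 = 0.004 | 1 − (1 − 0.00009)^30 × (1 − 0.00005)^30 = 0.4% |
| 10% | 0.42 × 0.10 = 0.04 | 1 − (1 − 0.0009)^30 × (1 − 0.0005)^30 = 4.1% |
| 10%, upper 95% limits | 0.91 × 0.10 = 0.09 | 8.7% |

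**The case against.** The strongest reply is that a permission and a duty can both be obeyed. Item 6 and 14.1.3 say that the participant can continue; they do not say that the participant must. A site that stops the drug breaches nothing. The 10.5.1 list is also not exclusive: Section 10.5 lists adverse events among the withdrawal reasons, and the synopsis lets the investigator withdraw a participant after an SAE. Item 6 itself points to Section 14, and the INR block in 14.1.4 sits under a heading for participants who meet a stopping criterion, which suggests that such SAEs were meant to be handled as stops. All of this stands, and it is why the point is minor.

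A reader might infer more than the text supports in two ways.

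- *That the protocol obliges a site to keep dosing through a liver SAE.* It does not. The wording is permissive, and the medical monitor is told within 24 hours on the 14.1.3 route.
- *That 14.1.3 and 14.1.4 contradict each other however the Section 14 trigger is read.* Twice-weekly tests satisfy a weekly minimum, and trial withdrawal comes only when follow-up is complete, so it does not clash with a permission to continue in the meantime.

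What the reply does not remove is that no sentence gives the SAE instruction precedence over 10.5.1. It also leaves to discretion a stop that Section 14, on its lead-in, makes immediate.

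**Conclusion.** The inconsistency is real but minor. For the case defined above, the protocol permits continued dosing in an event that it classes as a liver SAE. Elsewhere it either directs immediate withdrawal or, on the narrower reading of Section 14, contains no immediate stop. It states no order of precedence. A careful site would stop.

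The case is very rare. About 0.42 of 60 participants (0.17 to 0.91) would be expected to reach ALT of at least 3xULN from any cause, and the disputed case is a small part of that. The figure assumes that the earlier rates carry over to this trial. They probably overstate the risk: Section 11.2.2 says that most earlier losmapimod cases had confounding factors and arose in an acute coronary syndrome trial, and this trial excludes acute coronary syndrome in the last 6 months. The 1% to 10% share is an assumption with no support in the document. The case for a change rests on the rule trace and the low cost, not on expected frequency.

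**What to change.** Add one criterion to the 10.5.1 stopping list: *ALT ≥3xULN and INR >1.5, if INR is measured and the participant is not receiving anticoagulants.* Exclude that result from item 6 and from 14.1.3. The 14.1.3 reference to Section 10.5 then catches the case, whichever way the Section 14 trigger is read.

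The cost is a wording change in three places. INR stays optional, and no test, visit or change to the sample size is added.
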